**Table 1. S-1 initial standard dose and one-step dose reduction**

| Body surface area                              | Initial standard dose (FT equivalent)
(CCr ≥ 60) | Dose reduction level -1
(40 ≤ CCr < 60) |
|------------------------------------------------|-----------------------------------------------------|--------------------------------------------|
| < 1.25 m                           | 80 mg/day                                           | 50 mg/day                                  |
| ≥ 1.25 m  and < 1.5 m  | 100 mg/day                                          | 80 mg /day                                 |
| ≥ 1.5 m                            | 120 mg/day                                          | 100 mg /day                                |

**6.2.2. Criteria for starting administration (Arm A)**

At the start of the first administration, confirm that 4.1. selection criteria 6) are met on the day before or on the day of the start of administration and start administration.

If the criteria are not met, the start of administration should be postponed, and the first administration should be started after confirming that the relevant items meet the 4.1. selection criteria 6).

**6.2.3. Criteria for continuing administration (Arm A)**

After the first administration, S-1 administration will be suspended if the “Dose Continuation Criteria” in Table 2 are not met.

When it is confirmed that the “Criteria for continuing administration” in Table 2 are not met within 21 days of the first administration, S-1 should be suspended, and a reduced dose of S-1 should be considered from the next dose according to Table 5. Dose reduction levels.

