**6.2.4. Criteria for resumption of administration (Arm A)**

When restarting the drug after suspension, make sure that the “Criteria for resumption of administration” in Table 3 are met. However, if the adverse event meets the “Dose Reduction Criteria” in Table 4, the dose should be reduced from the time of resumption. If the drug is suspended due to an adverse event other than those listed in Table 2 “Criteria for continuing administration”, the grade of the adverse event that caused the suspension must have improved by at least one level, and the physician in charge must determine that the drug can be administered.

If S-1 treatment cannot be resumed after 28 days, protocol treatment should be discontinued.

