**Table 3. Criteria for resumption of administration**

| Item                                            | Criteria for resumption of administration                                                                        |
|-------------------------------------------------|------------------------------------------------------------------------------------------------------------------|
| White blood cell count                          | $\geq 3,000/\text{mm}^3$ and $\leq 12,000/\text{mm}^3$                                                           |
| Neutrophil count                                | $\geq 1,500/\text{mm}^3$                                                                                         |
| Platelet count                                  | $\geq 100,000/\text{mm}^3$                                                                                       |
| Total bilirubin                                 | $\leq 1.5\text{ mg/dL}$                                                                                          |
| AST and ALT                                     | $\leq 100\text{ IU/L}$                                                                                           |
| Creatinine                                      | $< 1.2\text{ mg/dL}$                                                                                             |
| Pneumonia                                       | Grade 0                                                                                                          |
| Infection                                       | No fever of suspected infection                                                                                  |
| PS                                              | 0 to 1                                                                                                           |
| Diarrhea, mouth ulcers                          | Grade 1 or below                                                                                                 |
| Other findings
and general clinical findings | Grade 2 or below
(However, the physician in charge may decide in his/her discretion to allow administration.) |

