**Table 9: Course Start Criteria (Arm B)**

| Item              |                        | Criteria for starting the course |
|-------------------|------------------------|----------------------------------|
| Blood toxicity    | White blood cell count | ≥ 3,000/mm           |
|                   | Neutrophil count       | ≥ 1,500/mm           |
|                   | Platelet count         | ≥ 100,000/mm         |
| Non-hematological | Total bilirubin        | ≤ 1.5 mg/dL                      |

|          |                                                |                                                                                         |
|----------|------------------------------------------------|-----------------------------------------------------------------------------------------|
| toxicity | AST and ALT                                    | $\leq 100$ IU/L                                                                         |
|          | Creatinine                                     | $< 1.2$ mg/dL                                                                           |
|          | Pneumonia                                      | Grade 0                                                                                 |
|          | Infection                                      | No fever with infection                                                                 |
|          | PS                                             | 0 to 1                                                                                  |
|          | Other subjective and general clinical findings | Grade 2 or below (but may be administered at the discretion of the physician in charge) |

[figure not shown]

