**Table 10. Criteria for decision of withdrawal of S-1 monotherapy**

| Item                       |                                | Criteria for withdrawal                                                                                                                                          | Criteria for resumption                                                                                          |
|----------------------------|--------------------------------|------------------------------------------------------------------------------------------------------------------------------------------------------------------|------------------------------------------------------------------------------------------------------------------|
| Blood toxicity             | White blood cell count         | $< 2,000/\text{mm}^3$                                                                                                                                            | $\geq 2,000/\text{mm}^3$                                                                                         |
|                            | Neutrophil count               | $< 1,000/\text{mm}^3$                                                                                                                                            | $\geq 1,000/\text{mm}^3$                                                                                         |
|                            | Platelet count                 | $< 75,000/\text{mm}^3$                                                                                                                                           | $\geq 75,000/\text{mm}^3$                                                                                        |
| Non-hematological toxicity | Total bilirubin                | $> 1.5$ mg/dL                                                                                                                                                    | $\leq 1.5$ mg/dL                                                                                                 |
|                            | AST and ALT                    | Greater than 100 IU/L                                                                                                                                            | 100 IU/L or less                                                                                                 |

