#### 6.3.4. Criteria for dose reduction (Arm B)

When resuming dosing in patients with adverse events that meet the criteria for dose reduction specified in Table 11, the dose should be reduced one step at a time according to Table 12, “Dose reduction levels”. However, the minimum dose of S-1 is 50 mg/day, and the dose will not be increased again after a dose reduction. For adverse events other than those listed in Table 11, the S-1 dose may be reduced at the discretion of the physician in charge, again in accordance with the dose reduction levels listed in Table 12.

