## **7. Protocol treatment discontinuation, termination criteria, and subsequent therapy**

### **7.1. Criteria for discontinuation of protocol treatment**

If any of the following criteria are met, the physician in charge will discontinue protocol treatment

- 1) If protocol treatment cannot be started 28 days after the last day of S-1 treatment (which corresponds to 21 days after the scheduled start of the next course in Arm B) (in this case, the day after the last day of S-1 treatment is considered Day 1). Starting administration on the same day of the week is acceptable).
- 2) If a withdrawal of more than 28 days is required (in this case, the day after the last day of S-1 administration shall be considered as Day 1. Resumption on the same day of the week 4 weeks after the date of the last dose is acceptable)
- 3) When an adverse event that meets each of the dose reduction criteria occurs even if the S-1 dose is reduced to the lowest level  
Or if a Grade 4 non-hematologic toxicity (Grade 1 or higher for pulmonary inflammation) develops.
- 4) When an adverse event occurs that makes it difficult to continue administration
- 5) If the physician in charge determines that the disease has recurred
- 6) If the patient requests discontinuation
- 7) When matters that should be excluded from the subjects turned out after registration
- 8) Other cases in which the physician in charge deems it necessary to discontinue the study.

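### A white cell count above 12,000/mm³ forces a hold, and after 28 days a stop, in Arm A only; Arm B has no such ceiling (minor)

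*Protocol*

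**What the plan says.** **Arm A.** Under Protocol 6.2.3, "S-1 administration will be suspended if the “Dose Continuation Criteria” in Table 2 are not met". Table 2 gives a WBC range of 2,000 to 12,000/mm³ for continuing. Table 3, which 6.2.4 makes a condition of restarting, gives 3,000 to 12,000/mm³. The clause in Table 3 that lets the physician allow dosing sits in the row for other findings, not in the WBC row. Section 6.2.4 then says: "If S-1 treatment cannot be resumed after 28 days, protocol treatment should be discontinued". Within the first 21 days, 6.2.3 adds that after a failed Table 2 criterion "a reduced dose of S-1 should be considered from the next dose according to Table 5".

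**Arm B.** Table 9 (course start) asks for a WBC of at least 3,000/mm³. Table 10 (within a course) withholds S-1 below 2,000/mm³ and allows it again from 2,000/mm³. Neither table has an upper limit. A high count can still be acted on, but only by choice: through the row for other events in Table 10, through 6.3.4 ("For adverse events other than those listed in Table 11, the S-1 dose may be reduced at the discretion of the physician in charge"), or through 7.1 items 4 and 8.

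**Both arms.** Entry requires a WBC of 3,000 to 12,000/mm³ (4.1 item 6). Suspected-infection fever leads to a hold in either arm during dosing. Section 7.1 discontinues protocol treatment "If a withdrawal of more than 28 days is required".

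**Endpoint.** Completion means six months of treatment with at least 70% of the planned dose. Only discontinuations due to recurrence leave the denominator (12.2). Section 13.4 selects an arm outright when its rate exceeds 40% and is more than 15 points higher than the other's.

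**The concern.** When the primary endpoint is completion, the rules for stopping treatment are part of how the endpoint is generated. They should differ between arms only where the schedules require it. Here a laboratory value with no evident link to the schedule leads to a mandatory hold, and possibly a mandatory stop, in one arm. In the other arm the physician decides. Where the rule acts, it turns Arm A patients into non-completers for a reason that does not bind in Arm B, and the completion rates feed directly into the choice of regimen for Phase III.

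**Working it through.** **1. Is the difference explained by the schedules?** Set the tables side by side.

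| Limit (per mm³) | Arm A | Arm B |
|---|---|---|
| WBC, continue or stay on | 2,000 to 12,000 (Table 2) | at least 2,000 (Table 10) |
| Neutrophils, same tables | 1,000 | 1,000 |
| Platelets, same tables | 75,000 | 75,000 |
| WBC, resume or start course | 3,000 to 12,000 (Table 3) | at least 3,000 (Table 9) |
| Neutrophils, same tables | 1,500 | 1,500 |
| Platelets, same tables | 100,000 | 100,000 |

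The dose-reduction criteria (Tables 4 and 11), reduction levels (5 and 12), escalation levels (6 and 13) and reductions after escalation (7 and 14) also agree. Having courses in one arm and continuous dosing in the other explains why the tables are applied at different times. It does not explain why only Arm A has a ceiling.

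**2. The plan's own figure.** Section 13.3 gives 37 per arm for 90% correct selection at 55% versus 40%. With exact binomials and ties split equally, P(A > B) + ½P(A = B) = 0.8824 + ½ × 0.0398 = 90.2% at 37 per arm, and 89.9% at 36. The figure reproduces.

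**3. Can holds alone make a non-completer?**
- Planned Arm A dosing days in six months: 4 per week × 26 weeks = 104.
- The longest permitted hold (restart on the same weekday four weeks after the last dose) misses 4 × 4 − 1 = 15 days: 89/104 = 85.6%.
- Two such holds miss 30 days: 74/104 = 71.2%.
- 31 missed days: 73/104 = 70.2%. 32 missed days: 72/104 = 69.2%.

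At full dose, the ratio falls below 70% only after 32/4 = 8 weeks of holds. The practical route to non-completion is therefore the 28-day stop.

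**4. What does one stopped patient cost?**
- If the patient would otherwise have completed: 1/50 = 2.0 points (100 patients, equal allocation assumed) to 1/37 = 2.7 points.
- If completion was uncertain, weighted by the plan's assumed rates: 0.40 × 2.0 = 0.8 to 0.55 × 2.7 ≈ 1.5 points expected.

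**5. Illustration with assumed losses.** The protocol gives no frequency of a WBC above 12,000/mm³. Suppose Arm A is truly the 55% arm, with 37 per arm.
- Losing 2% of its would-be completers (0.02 × 0.55 × 37 ≈ 0.4 patients) gives 0.55 × 0.98 = 53.9%, and correct selection falls from 90.2% to 88.5%.
- Losing 5% (0.05 × 0.55 × 37 ≈ 1.0 patient) gives 52.3% and 85.5%.

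These figures are for picking the arm with the higher observed rate. They do not include the 15-point margin in 13.4, and neither percentage is an estimate.

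**The case against.** The route to harm is narrow. A patient needs a WBC above 12,000/mm³ for more than 28 days within the first six months, without suspected-infection fever and without recurrence, and must have been going to complete otherwise. Standing leukocytosis is screened out at entry, and 6.2.2 checks again before Arm A's first dose. All of this stands, and it is why the point is minor.

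The two rule sets also differ in other ways. Arm B must meet the stricter low-count limits at every course start, whereas an unsuspended Arm A patient continues on the looser ones. In the other direction, Arm A's resumption limits are stricter than Arm B's in-course limits. A reader might infer that the protocol's management rules as a whole disadvantage Arm A. The document does not support that; only the WBC ceiling, taken alone, acts against Arm A.

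Three other stronger readings also fail:
- *The 28-day stop exists only in Arm A.* Section 7.1 applies it to both arms. What differs is that a high WBC must lead to it in Arm A and need not in Arm B.
- *A high WBC forces a dose reduction in Arm A.* The 21-day sentence in 6.2.3 is a prompt to consider one, and high WBC is not a reduction criterion in Table 4.
- *Arm B starts treatment unchecked.* Sections 11.1, 11.3 and 11.4 schedule the tests in both arms, and Table 9 probably covers course 1. What 6.3.2 lacks is the explicit instruction in 6.2.2 to postpone the first dose if 4.1 item 6 is not met.

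The objection does not supply a reason for the ceiling in one arm. Physician discretion in Arm B is not equivalent to a mandatory rule in Arm A.

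**Conclusion.** The inconsistency is real and clear on the text: a persistently high WBC ends protocol treatment by rule in Arm A and only by judgement in Arm B. A patient stopped this way in the first six months counts against Arm A on the primary endpoint. Severity is minor. No shift in the completion rate can be claimed, because the frequency is not stated and is probably very low. Per stopped patient the loss is 2.0 to 2.7 points if that patient would otherwise have completed, or about 0.8 to 1.5 points in expectation at the plan's assumed 40–55% completion. The lower end of each range assumes equal allocation of 100 patients and the upper end uses 37 per arm. Confidence is high for the textual difference, not for any practical effect on the selection.

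**What to change.** Use the same WBC limits in both arms, in one of two ways:
- **Delete the upper limit of 12,000/mm³ from Tables 2 and 3.** A high WBC without fever would no longer force a hold in Arm A, but the infection-fever and pneumonia rows remain. This also takes high WBC out of the 21-day prompt in 6.2.3.
- **Add the same upper limit to Tables 9 and 10.** The downside is a few more holds or postponements in Arm B.

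Optionally, state in 6.3.2 that Arm B's first dose also requires 4.1 item 6 to be met, as 6.2.2 does for Arm A.

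The cost is a table row and a sentence. No new tests are needed, since blood counts are already scheduled in both arms.

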**Table 2. Criteria for continuing administration**

| Item                           | Criteria for continuing administration                                                                                                                           |
|--------------------------------|------------------------------------------------------------------------------------------------------------------------------------------------------------------|
| White blood cell count         | ≥ 2,000 /mm  and ≤ 12,000 /mm                                                                                                            |
| Neutrophil count               | ≥ 1,000 /mm                                                                                                                                          |
| Platelet count                 | ≥ 75,000 /mm                                                                                                                                         |
| Total bilirubin                | ≤ 1.5 mg/dL                                                                                                                                                      |
| AST and ALT                    | ≤ 100 IU/L                                                                                                                                                       |
| Creatinine                     | < 1.2 mg/dL                                                                                                                                                      |
| Pneumonia                      | Grade 0                                                                                                                                                          |
| Infection                      | No fever of suspected infection                                                                                                                                  |
| PS                             | 0 to 1                                                                                                                                                           |
| Diarrhea, mouth ulcers         | Grade 1 or below                                                                                                                                                 |
| Other non-hematologic toxicity | Grade 2 or below
(However, the physician in charge may decide in his/her discretion to allow administration.)                                                 |
| Others                         | Drug withdrawal is allowed when deemed necessary by the physician in charge due to the occurrence of adverse events that do not fall under the above categories. |

**6.2.4. Criteria for resumption of administration (Arm A)**

When restarting the drug after suspension, make sure that the “Criteria for resumption of administration” in Table 3 are met. However, if the adverse event meets the “Dose Reduction Criteria” in Table 4, the dose should be reduced from the time of resumption. If the drug is suspended due to an adverse event other than those listed in Table 2 “Criteria for continuing administration”, the grade of the adverse event that caused the suspension must have improved by at least one level, and the physician in charge must determine that the drug can be administered.

If S-1 treatment cannot be resumed after 28 days, protocol treatment should be discontinued.

**Table 3. Criteria for resumption of administration**

| Item                                            | Criteria for resumption of administration                                                                        |
|-------------------------------------------------|------------------------------------------------------------------------------------------------------------------|
| White blood cell count                          | $\geq 3,000/\text{mm}^3$ and $\leq 12,000/\text{mm}^3$                                                           |
| Neutrophil count                                | $\geq 1,500/\text{mm}^3$                                                                                         |
| Platelet count                                  | $\geq 100,000/\text{mm}^3$                                                                                       |
| Total bilirubin                                 | $\leq 1.5\text{ mg/dL}$                                                                                          |
| AST and ALT                                     | $\leq 100\text{ IU/L}$                                                                                           |
| Creatinine                                      | $< 1.2\text{ mg/dL}$                                                                                             |
| Pneumonia                                       | Grade 0                                                                                                          |
| Infection                                       | No fever of suspected infection                                                                                  |
| PS                                              | 0 to 1                                                                                                           |
| Diarrhea, mouth ulcers                          | Grade 1 or below                                                                                                 |
| Other findings
and general clinical findings | Grade 2 or below
(However, the physician in charge may decide in his/her discretion to allow administration.) |

